# Effectiveness of individualized physiotherapy on pain and functioning compared to a standard exercise protocol in patients presenting with clinical signs of subacromial impingement syndrome. A randomized controlled trial

**DOI:** 10.1186/1471-2474-11-114

**Published:** 2010-06-09

## Abstract

**Background:**

Shoulder impingement syndrome is a common musculoskeletal complaint leading to significant reduction of health and disability. Physiotherapy is often the first choice of treatment although its effectiveness is still under debate. Systematic reviews in this field highlight the need for more high quality trials to investigate the effectiveness of physiotherapy interventions in patients with subacromial impingement syndrome.

**Methods/Design:**

This randomized controlled trial will investigate the effectiveness of individualized physiotherapy in patients presenting with clinical signs and symptoms of subacromial impingement, involving 90 participants aged 18-75. Participants are recruited from outpatient physiotherapy clinics, general practitioners, and orthopaedic surgeons in Germany. Eligible participants will be randomly allocated to either individualized physiotherapy or to a standard exercise protocol using central randomization.

The control group will perform the standard exercise protocol aiming to restore muscular deficits in strength, mobility, and coordination of the rotator cuff and the shoulder girdle muscles to unload the subacromial space during active movements. Participants of the intervention group will perform the standard exercise protocol as a home program, and will additionally be treated with individualized physiotherapy based on clinical examination results, and guided by a decision tree. After the intervention phase both groups will continue their home program for another 7 weeks.

Outcome will be measured at 5 weeks and at 3 and 12 months after inclusion using the shoulder pain and disability index and patients' global impression of change, the generic patient-specific scale, the average weekly pain score, and patient satisfaction with treatment. Additionally, the fear avoidance beliefs questionnaire, the pain catastrophizing scale, and patients' expectancies of treatment effect are assessed. Participants' adherence to the protocol, use of additional treatments for the shoulder, direct and indirect costs, and sick leave due to shoulder complaints will be recorded in a shoulder log-book.

**Discussion:**

To our knowledge this is the first trial comparing individualized physiotherapy based on a defined decision making process to a standardized exercise protocol. Using high-quality methodologies, this trial will add evidence to the limited body of knowledge about the effect of physiotherapy in patients with SIS.

**Trial registration:**

Current Controlled Trials ISRCTN86900354

## Background

Shoulder complaints are one of the most common musculoskeletal complaints seen by health professionals [1-5] with an incidence of 9.5 per 1000 patients presenting to primary care [6] and varying data for point prevalence (6.9% to 26%) [7]. They can lead to a significant reduction of health [6,8], seem to be recurring in nature and do not necessarily resolve over time [9-12]. Thus, shoulder complaints represent a relevant health problem for clinicians, employers and health insurance companies.

Although no standardized diagnostic classification for shoulder complaints exists, most shoulder patients presenting to primary care show clinical signs of subacromial impingement [5,6]. Subacromial impingement syndrome of the shoulder (SIS) occurs due to a mechanical disturbance within the subacromial space and is characterized by pain and functional restrictions mostly during overhead activities in daily life or sporting activities [13]. Potential factors causing or contributing to SIS such as strength, coordination and integrity of the rotator cuff [14-21] and the shoulder girdle muscles [22-26], mechanical or anatomical changes [27-29], hypomobility or instability of the glenohumeral joint or the scapula [16,26,30-33], and the influence of posture [34,35] are discussed in the literature and suggest a multi-factorial aetiology of SIS. Besides the biomedical aspects of SIS, psychological factors such as kinesiophobia or catastrophizing may negatively influence recovery and thus leading to chronic pain and disability [36-41]. The specific diagnosis of SIS is often based on a thorough history and clinical examination; technical examination methods such as MRI or ultrasonography are often not used in first instance [10], also because their diagnostic accuracy is still limited [42-47].

Physiotherapy is often the first choice of treatment for SIS. Between 10 to 30% of all shoulder patients seen in primary care are referred to physiotherapy after initial presentation [5,10,48]. However, the effectiveness of physiotherapy in patients with SIS is still under debate. Conclusions from systematic reviews suggest that physiotherapy-led interventions, combining different methods or techniques, are not more effective than exercises alone except adding manual mobilization to exercises, which seems to be of additional benefit. Most technical treatments such as ultrasound or laser therapy cannot be recommended. However evidence is limited by poor methodological quality, short follow ups and small sample sizes [49-52]. Thus nearly all current systematic reviews emphasize the need for more high quality trials of physiotherapy interventions, especially of combination of treatment techniques.

This trial compares individualized physiotherapy (IP), considering the patients' individual situation, bio-psycho-social aspects, and the WHO-classification of functioning and disability [53] to a standardized exercise protocol (SEP). Physiotherapeutic management is based on clinical examination results and guided by a defined clinical reasoning process, which belongs to one of the basic skills in musculoskeletal physiotherapy [54].

### Aims of the study

a) To investigate the effect of individually planned physiotherapy (IP) on pain and functioning compared to a standard exercise protocol (SEP) in patients presenting with clinical signs of SIS.

b) To compare direct and indirect costs between both interventions.

## Methods

### Study design

To answer the questions a randomized controlled trial design will be used over a 12 months period. Patients will be randomized after providing informed consent. Randomization and all communication about it is executed and controlled by the Department of Epidemiology, Maastricht University. A flow chart of the trial profile is provided in Figure 1.

**Figure 1 F1:**
[figure not shown]
**Trial profile**.

### Ethics

Ethical approval for this trial has been granted by the Medical Ethics Committee of the Munich University Hospital, Ludwig-Maximilians-University Munich, Germany.

### Eligibility criteria

Patients presenting to primary care with clinical signs and symptoms indicating SIS will be included in the trial. This concept of focusing on important clinical signs for setting up inclusion criteria for a RCT corresponds well with daily clinical practice.

Inclusion criteria: (1) age between 18 and 75 years, (2) symptoms for more than four weeks, (3) main complaints in the glenohumeral joint region or the proximal arm, (4) presence of one of the following signs indicating SIS: Neer impingement test, Hawkins-Kennedy impingement test, painful arc with active abduction or flexion, (5) pain with one of the following resistance tests: external rotation, internal rotation, abduction, or flexion.

Exclusion criteria: (1) average 24-hours pain of 8/10 or more on a visual numeric rating scale (VNRS), (2) primary scapulothoracic dysfunction due to paresis, (3) diagnosed instability or previous history of dislocation, (4) adhesive capsulitis (frozen shoulder), (5) more than 1/3 restriction of elevation compared to the unaffected side, (6) substantial shoulder weakness or loss of active shoulder function, (7) shoulder surgery in the last 12 months on the involved side, (8) reproduction of symptoms with active or passive cervical movements, (9) neurological involvement with sensory and muscular deficit, (10) inflammatory joint disease (e.g. rheumatoid arthritis), (11) diabetes mellitus, (12) intake of psychotherapeutic drugs, (13) compensation claims, (14) inability to understand written or spoken German.

### Recruitment of participants

The proposed trial will be embedded in the normal daily process of selected physiotherapy clinics in Germany. Participants will be identified by physiotherapy referrals and by research physiotherapists. If a patient agrees to participate, the research therapist will check eligibility criteria. If eligibility is confirmed, informed consent will be asked. Participants will then undergo baseline assessment including some questionnaires and a standardized clinical examination protocol for the shoulder complex, the cervical and upper thoracic spine.

An inclusion period of eighteen months is thought to be sufficient to recruit the number of participants needed for this study.

### Randomization and allocation concealment

After informed consent and baseline assessment participants will be randomized to either SEP or IP using block allocation of six. To guarantee allocation concealment, therapists will be informed about allocation after the participant completed all baseline measurements and gave informed consent, prior to first treatment by the Department of Epidemiology, Maastricht University.

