### Sample size

Sample size for this trial is based on an expected difference between groups of a 13 points reduction of the SPADI score. The statistical level of significance was set to alpha = 0.05, statistical power to 80%, and a 15% drop out rate was expected. The assumed standard deviation was set to 20 points based on the results of other studies [117-120]. Power calculations resulted in an estimated sample size of 90 participants (45 per group) to detect a 13 points difference in SPADI score. The minimum clinically important change is set to an 11 points improvement in total SPADI score [93].

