## Results

Inclusion of participants has started in April 2010. First results are expected in 2012, long term results in 2013.

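### A single fixed block of six, published while recruitment was open, leaves some later allocations predictable to any screening therapist who knows the earlier ones

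*Protocol article*

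**What the plan says.** Under Randomization and allocation concealment, the protocol article states that "participants will be randomized to either SEP or IP using block allocation of six". To secure concealment, "therapists will be informed about allocation after the participant completed all baseline measurements and gave informed consent", before the first treatment, with the assignment released by a remote university department. The article presents this procedure as a guarantee, and its Discussion relies on it to prevent selection bias.

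Under Recruitment of participants, patients are identified through referrals and by research physiotherapists at selected clinics: "If a patient agrees to participate, the research therapist will check eligibility criteria". The inclusion period is eighteen months. The Results section reports: "Inclusion of participants has started in April 2010". The article itself is dated 9 June 2010.

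Only the statistician is described as blinded to group (Discussion). Therapists treating the control group are blinded to the examination findings, not to the allocation (Control group). Therapists meet monthly (Interventions, Both groups).

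**The concern.** Telling therapists the assignment only after enrolment protects that patient's assignment. It does nothing for the next patient if the block length is constant and known, because a person who has counted the earlier assignments in a block can work out some of the remaining ones. The length was public for most of the planned recruitment.

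Selective enrolment is what is at stake. Several eligibility criteria need judgement from the screening therapist: pain on resistance testing, restriction of elevation by more than a third, substantial weakness. The treating therapists are qualified in manual therapy and the article calls the individualized arm a best-practice approach, so a preference about who receives it is plausible. A guess about the next arm could then influence who is enrolled, and adjustment for measured baseline variables cannot fully repair selection on unmeasured prognosis.

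**Working it through.** **Inputs from the article.** Block of six; two arms of 45, 90 in total; difference of 13 SPADI points; SD 20; "The statistical level of significance was set to alpha = 0.05, statistical power to 80%, and a 15% drop out rate was expected". Assumptions: two-sided alpha; three patients per arm in each block (from the equal arms); number of clinics between 1 and 10, each patient equally likely to come from any of them.

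**The plan's own figure.** n per group = 2 × [20 × (1.960 + 0.842) / 13]² = 37.15, rounded up to 38. With 15% dropout, 38 / 0.85 = 44.7, so 45 per group and 90 in total. The stated size is reproduced. It equals 90 / 6 = 15 complete blocks, and nothing below changes it.

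**Allocations certain in advance, whole sequence known.** A block of 3 + 3 has 20 possible orders. An allocation is forced once the other arm is full, so the number forced equals the length of the last run. Of the 20 orders, 12 end in a run of one, 6 in a run of two and 2 in a run of three:

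(12 × 1 + 6 × 2 + 2 × 3) / 20 = 30 / 20 = 1.5 of 6, or 25%. Over 90 patients that is 0.25 × 90 = 22.5.

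**Correct guesses, whole sequence known.** The observer always names the arm that is behind and tosses a coin when the arms are level. Three of the six steps in a block move back towards balance, and all three are guessed correctly. Steps taken from balance are right half the time. Balance holds at the start (probability 1), after two allocations (12/20 = 0.6) and after four (0.6), so 2.2 times per block on average:

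3 + 2.2 / 2 = 4.1 of 6, or 68.3%, against 50% by chance.

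**Correct guesses, one central list shared, own clinic seen only.** Simulation of 90 allocations from fixed blocks of six, with patients falling at random across clinics:

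| Clinics | Guess from own-clinic running imbalance | Guess the opposite of the last own-clinic allocation |
|---|---|---|
| 2 | about 53% | about 57% |
| 3 | about 53% | about 55% |
| 5 | about 52% | about 54% |
| 10 | about 51% | about 52% |

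These are simple guessing rules, not proven optimal ones. The range is about 51% to 57%. If lists ran per clinic, or therapists pooled what they know, the figures would return to 25% and 68.3%.

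**After the change.** Random blocks of 4, 6 and 8, with an observer who sees the full sequence, knows the set of sizes and updates by Bayes' rule:

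| | Fixed six | Random 4/6/8 |
|---|---|---|
| Certain in advance | 25% | about 2.4% |
| Guessed correctly | 68.3% | about 67.9% |

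**The case against.** The strongest defence is that the article describes central randomization by a remote department over several clinics, with no blocking by clinic mentioned. A therapist who sees only local patients then sees fragments of the list, and guessing is not far above chance. This stands, and it is why 25% and 68% can only be upper bounds.

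A reader might infer that the therapists who screen learn every allocation. The text says only that therapists are informed about allocation. It does not say that the screener is the one informed, or that anyone sees the whole sequence. A reader might also assume that the screener and the treating therapist are the same person. The blinding of control-arm therapists to examination findings points to some separation of roles, at least for control patients. Sharing at the monthly meetings is possible, but the article does not describe it.

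A further argument is that outcomes are self-reported by patients who know their treatment. That concerns outcome reporting, does not follow from block length, and adds no weight here.

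Finally, varying the block size barely changes average guessing success. This is correct and limits what the remedy can be said to achieve. It does not remove the case for it, because certain foreknowledge is the clearest opening for selective enrolment and that is what falls.

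None of this rescues the guarantee. A single block length, disclosed during recruitment, is a stated choice and not a detail left to another document.

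**Conclusion.** The point holds in a limited form. Late release conceals the current assignment but does not guarantee concealment of later ones when one fixed block length is public and therapists are told allocations. The exposure depends on how much screening therapists know of earlier allocations. It runs from about 51% to 57% correct guesses (one shared list, own clinic only, 2 to 10 clinics) up to 68%, with 25% of allocations certain, if the full sequence is known. Where this trial lies in that range cannot be settled from the article, because the number of clinics, the recipient of the allocation and the unit of blocking are not stated. The documents do not show that any allocation was in fact predicted. The sample size is unaffected.

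**What to change.** For all remaining allocations, the central office should draw randomly varying block sizes (for example 4, 6 and 8 in random order) and disclose neither the sizes nor their set until recruitment closes. The description of the procedure should claim concealment of the current assignment and not a guarantee for the sequence.

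The benefit should be stated narrowly: fewer allocations known with certainty, from 25% to about 2% for a full-sequence observer who knows the sizes, with average guessing success still near 68%. The cost is a new list at the central office and a possible imbalance of a few patients if recruitment stops inside a block, at most half the largest block (8 / 2 = 4). No clinical procedure changes.

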### Interventions

#### Both groups

All participants will undergo a clinical examination process starting with a thorough history taking, followed by a physical examination of the cervical spine, the shoulder girdle, and the shoulder joints. All joints are manually assessed with passive, active, and combined angular movements, and with translatory tests according to the description of Kaltenborn [55], Evjenth and Hamberg [56] or Maitland [57]. Isometric resistance tests are used to judge shoulder strength and pain. Integrity of the rotator cuff is assessed with the external rotation lag sign [58], the lift off test [59], and the hornblowers' sign [60]; involvement of the neural system with upper limb tension tests described by Butler [61]. Contributing factors such as a slouched posture, forward head position, thoracic kyphosis, or protracted shoulders are noted and if necessary also assessed in detail. Results serve as basis for the treatment of participants allocated to the group receiving individualized physiotherapy.

All participants will attend two 20-30 minute contact sessions per week over a 5 week period. Afterwards participants will continue with their home exercises for another 7 weeks. At the beginning of treatment all participants will receive an information booklet containing basic information about anatomy and biomechanics of the shoulder complex, a short description of the aetiology of SIS and the pathology itself, and a brief overview about possible contributing factors to their shoulder pain. The booklet also explains the goals to be achieved with treatment, and it provides general guidelines for behaviour through daily living. Participants will also receive a shoulder log book for documentation of their weekly pain levels, additional treatments or medication, sick leave, and the completion of the home exercise during the intervention phase and during the follow up period. Participants will be requested not to make use of other treatment options and not to change their medication intake during the intervention phase. However, due to ethical considerations the use of analgesics and non-steroidal anti-inflammatory drugs will be permitted and will be recorded in the shoulder log-book.

Treatment will be administered by experienced physiotherapists with an international qualification for manual therapy (IFOMPT standard). All physiotherapists will be trained prior to commencement of the study to guarantee a uniform background and treatment application. A written manual with detailed and comprehensive instructions is given to the therapists. Thoroughness of the application is supported by structured recording forms and check lists, monthly team meetings and audits.

The two groups are as follows:

#### Control group

Participants assigned to the control group will perform a standard exercise protocol (SEP) aiming at restoring muscular deficits in strength, mobility, or coordination of the rotator cuff and the shoulder girdle, unloading the subacromial space, and centering the humeral head in the glenoid fossa during active movements. Thus, the SEP contains mainly strengthening exercises, stretching and mobility exercises, but also exercises to control pain. To set up a high quality protocol, exercises are taken from papers investigating exercises for shoulder rehabilitation [62-79], and exercises specifically addressing deficits in strength, mobility, or coordination revealed in patients with SIS [19,23-25,31,80,81]. Another important criterion for the selection of the exercises was their practicability, their potential for pain provocation, and the possibility to perform all exercises at home with a rubber band. Exercises are subdivided in a "core program" and "additional exercises". A short description of the exercises is provided in Table 1 &2.

**Table 1 T1:** Exercises of the core program.

**No**.	Exercise	Material	Description
C1a	Low row	Pinoband or pulley apparatus with 2 handles	Subject is sitting in front of pinoband, shoulders in 80° forward flexion and neutral rotation; subject performs shoulder extension with elbows flexed.

C1b	High row	Pinoband or pulley apparatus with 2 handles	Subject is sitting in front of pinoband, shoulders in 100° forward flexion and neutral rotation; subject performs shoulder extension with elbows extended.

C2	Shoulder adduction in scapular plane	Pinoband or pulley apparatus with 1 handle	Subject is standing, shoulder in 80° abduction in scapular plane; subject performs shoulder adduction with elbow extended.

C3a	Shoulder external rotation in 0° abduction	Pinoband or pulley apparatus with 1 handle	Subject is standing, with towel between arm and trunk to prevent compensatory shoulder movements, elbow flexed to 90°; subject performs shoulder external rotation.

C3b	Shoulder external rotation in side-lying	Dumbbell	Subject is side-lying, with towel between arm and trunk to prevent compensatory shoulder movements, elbow flexed to 90°; subject performs shoulder external rotation.

C4a	Shoulder internal rotation in 0° abduction	Pinoband or pulley apparatus with 1 handle	Subject is standing, with towel between arm and trunk to prevent compensatory shoulder movements, elbow flexed to 90°; subject performs shoulder internal rotation.

C4b	Shoulder internal rotation in side-lying	Dumbbell	Subject is side-lying, elbow flexed to 90°; subject performs shoulder internal rotation.

C5	Elbow flexion with forearm supination	Pinoband or dumbbell	Subject standing arm at the side, neutral rotation; subject performs elbow flexion/forearm supination.

C6a	Horizontal scapular protraction	Pinoband or pulley apparatus with 2 handles	Subject is standing, elbows flexed to 90°; subject performs shoulder flexion to 80° and elbow extension, then scapular protraction.

C6b	Vertical scapular protraction	Pinoband or dumbbells	Subject lying supine, elbows flexed to 90°; subject performs shoulder flexion to 90° and elbow extension, then scapular protraction.

C7	4-point kneeling scapular protraction	-	Subject in 4-point kneeling position, hands underneath shoulders performs dynamic scapular protraction.

C8	Scapular setting	-	Subject lying prone with arms held by the side in external rotation; subject holds scapulae in depressed and retracted position.

C9	Posterior shoulder stretch	-	Subject is standing, pulling the elbow passively across the body into horizontal adduction with the opposite arm.

C10	Lateral neck stretch	-	Subject is standing, pulling the head into lateral flexion with the opposite arm and is adding the shoulder depression to stretch the ipsilateral neck.

C11	Thoracic spine extension	-	Supine on the floor, hips and knees flexed to 90 degrees, hands supporting the neck, with thoracic kyphosis lying on a towel roll.

**Table 2 T2:** Additional exercises.

No.	Exercise	Material	Description
A1a	Shoulder abduction in scapular plane (scaption)	Pinoband or dumbbell	Subject is standing with feet on the pinoband; subject performs 80° of scaption with elbows slightly flexed and external rotation of the shoulder (thumb up).

A1b	Shoulder flexion	Pinoband or dumbbell	Subject is standing with feet on the pinoband; subject performs 80° of shoulder flexion with elbows slightly flexed and external rotation of the shoulder (thumb up).

A2a	Shoulder press via flexion	Pinoband or dumbbell	Subject is sitting with back supported. Upper arms are in contact with the trunk, elbows are maximally flexed and hands in front of shoulders; subject performs full shoulder flexion and elbow extension.

A2b	Shoulder press via abduction	Pinoband	Subject is sitting with back supported. Upper arms are in contact with the trunk, elbows are maximally flexed and hands next to shoulders; subject performs full shoulder abduction and elbow extension.

A3	Horizontal abduction	Pinoband or pulley apparatus with 1 handle	Subject is sitting in front of pinoband attached in shoulder height, shoulders in 80° forward flexion and external rotation; subject performs horizontal shoulder abduction with nearly extended elbows.

A4	External rotation in supported 80° shoulder flexion	Pinoband or pulley apparatus with 1 handle	Subject is sitting with elbow supported on a table in 80° of shoulder flexion and 90° elbow flexion. Pinoband fixed on the table with other hand; subject performs 90° of external rotation.

A5	Internal rotation in supported 80° shoulder flexion	Pinoband or pulley apparatus with 1 handle	Subject is sitting with elbow supported with the other hand in 80° of shoulder flexion, pinoband fixed in waste height; subject performs 90° of internal rotation.

A6a	Shoulder protraction in kneeling push up position	-	Subject in kneeling push up position, hands underneath shoulders and knees behind hips; subject performs dynamic scapular protraction.

A6b	Shoulder protraction in push up position	-	Subject in push up position; subject performs dynamic scapular protraction.

A6c	Half way push up plus	-	Subject in push up position; subject performs a half way push up with a dynamic scapular protraction at the end of arm extension.

AM1	Internal rotation positioning	-	Subject is placing the hand on the buttock or lower back in a pain-free manner, supported by the other hand.

AP1	Pendulum exercises	Dumbbell or bottle	Subject is standing leaning on a chair or table with the good arm and bending forward at the waist. Relax the shoulder blade and let it drop. Subject performs relaxed forward-backward swings and circle swings using body motion.

AP2	Longitudinal shoulder traction	Pinoband	Subject is standing and slightly side bent with pinoband is wrapped around the wrist and fixed with the feet on the bottom with tension. Subject is relaxing the shoulder to allow for longitudinal traction.

Exercises of the "core program" are introduced and instructed to the patient in detail first, and if patients show good progression, exercises from the pool of "additional exercises" can be added. At home exercises are realized with the help of a PINOFIT rubber band (Pino GmbH, Hamburg, Germany) which allows dynamic resistance and is easy to use. It is available from very light resistance to heavy resistance and allows the therapist to progressively adapt resistance to the physical capacity of the patient. Patients are supervised during their contact sessions; their exercise program is monitored, controlled and adapted if necessary. Physiotherapists are allowed to adapt the SEP individually to each patient with respect to the situation of the patient. Therapists who deliver the treatment for the control group remain blinded to the clinical examination results to prevent inadvertent contamination of the SEP.

